## Abstract

**Background:**

Pressure ulcers are insidious complications that affect approximately 2.5 million patients and account for approximately US$11 billion in annual health care spending each year. To date we are unaware of any study that has used a wearable patient sensor to quantify patient movement and positioning in an effort to assess whether adherence to optimal patient turning results in a reduction in pressure ulcer occurrence.

**Methods/design:**

This study is a single-site, open-label, two-arm, randomized controlled trial that will enroll 1812 patients from two intensive care units. All subjects will be randomly assigned, with the aid of a computer-generated schedule, to either a standard care group (control) or an optimal pressure ulcer-preventative care group (treatment). Optimal pressure ulcer prevention is defined as regular turning every 2 h with at least 15 min of tissue decompression. All subjects will receive a wearable patient sensor (Leaf Healthcare, Inc., Pleasanton, CA, USA) that will detect patient movement and positioning. This information is relayed through a proprietary mesh network to a central server for display on a user-interface to assist with nursing care. This information is used to guide preventative care practices for those within the treatment group. Patients will be monitored throughout their admission in the intensive care unit.

**Discussion:**

We plan to conduct a randomized control trial, which to our knowledge is the first of its kind to use a wearable patient sensor to quantify and establish optimal preventative care practices, in an attempt to determine whether this is effective in reducing hospital-acquired pressure ulcers.

**Trial registration:**

ClinicalTrials.gov, NCT02533726.

## Background

Pressure ulcers are insidious complications that affect approximately 2.5 million patients and account for approximately US$11 billion in annual health care spending each year [1]. Acutely ill patients are at risk for the development of pressure ulcers due to immobility, reduced perfusion, and prolonged duration of mechanical ventilation [2]. In 2008 the Centers for Medicare and Medicaid Services discontinued reimbursement for facility-acquired pressure ulcers (also known as hospital-acquired pressure ulcers, HAPUs), as these are considered an avoidable complication often described as a “never event.” Given the tremendous burden that pressure ulcers place on the individual patient and the health care system, there is a substantial need for improved prevention methods [3, 4].

Pressure ulcers form when there is sustained pressure, predominately over bony prominences such as the sacrum, heels, occiput, and shoulders. Unrelieved pressure causes compression of cellular tissue, impaired blood flow, and can lead to localized tissue damage and cellular death. Pressure ulcers initially appear as areas of reddened skin but can quickly develop into large open wounds if the pressure is not relieved.

To prevent pressure ulcers, the currently accepted standard of care is to turn patients at least every 2 h, day and night. However, there are no published research studies that support the every 2-h turning schedule in critically ill patients. Notwithstanding, studies have estimated that compliance with patient-turning protocols are around 60 % and that a significant number of patients are not being turned as frequently as recommended [5, 6]. In intensive care units (ICUs), compliance to turning protocols is even lower, ranging from 38 to 51 % [7, 8]. Potential explanations for this low compliance include low prioritization of turning, difficulty in monitoring a patient’s position, ineffective turn reminders/alerts, and sub-optimal caregiver staffing ratios – all of which hinder efforts to prevent pressure ulcers.

To improve adherence to turning as a preventative practice, Leaf Healthcare Inc. (Pleasanton, CA, USA) has developed a patient-monitoring system designed to optimize patient-turning practices. This system is composed of a small, single, wearable patient sensor that adheres to a patient’s chest, similar to a standard telemetry electrode. The sensor communicates wirelessly to a central monitoring station about the patient’s current position (upright, supine/back, right side, left side) and time-to-next-turn. Data for all patients are displayed on a User-Dashboard, allowing staff to easily identify patients who are in need of turning. The system also allows caregivers to identify restricted positions due to existing pressure ulcers or surgical wounds, as well as to create personalized turning protocols, by varying the degree of turn angle and/or tissue decompression thresholds.

Two single-center clinical studies have been completed using the monitoring equipment. A small first-in-human Institutional Review Board (IRB)-approved study was performed to test the feasibility of the patient sensor, mesh network, and monitoring system, and to collect baseline data regarding turning protocol compliance. After this, a second single-center IRB-approved clinical study tested the efficacy, usability, and safety of the monitoring system (ClinicalTrials.gov #NCT02005692). After implementation of the system, compliance to patient turning was reported to have increased significantly from 64 to 98 % [9].

To date, the study team are unaware of any study that has used a wearable patient sensor to quantify patient movement and positioning, in an effort to assess whether adherence to optimal patient turning results in a reduction in pressure ulcer occurrence. As such, the following protocol describes the study to be conducted to evaluate whether optimal patient turning, defined as regular turning every 2 h with at least 15 min of tissue decompression, reduces HAPUs in acutely ill patients.

## Methods/design

### Design

This study is a single-site, open-label, two-arm, randomized controlled trial. As this is an open-label trial, a short observation pilot study will be undertaken during installation and testing of the patient-monitoring system to account for potential observer bias (the Hawthorne effect). The true intent of the technology will be obfuscated to patients and clinical staff in an effort to record baseline data that more accurately represent current turning practices within these units. These pilot data will also be used to determine minimum turning thresholds for the main study and to assess the representativeness of the main study’s control group. A convenient sample of 25 subjects will be enrolled from each participating unit.

### Randomization

All subjects will be randomly assigned, with the aid of a computer-generated schedule, to receive either standard care (control group) or optimal pressure ulcer preventative care (treatment group). To minimize the risk of predicting the treatment assignment, randomization is performed in permuted blocks of two, four, and six, with random variation of block sizes. To minimize bias at the patient level, randomization is further stratified by unit of admission and admitting service, either medicine or surgery (Fig. 1). Once randomized, each subject will receive a nominal study identification number based on the unit of admission and admitting service. The lowest available number will be provided to each subject in sequential order.

**Fig. 1 Fig1:**
[figure not shown]
Randomization schema. Stratification by unit and admitting service team

### Study population

This study will enroll all patients admitted to two ICUs. These patients are critically ill with exacerbations of acute and chronic medical conditions, or are receiving aggressive post-surgical care for neurological, cardiac, or trauma-related conditions. They typically have altered levels of consciousness and are dependent on clinical staff for activities of daily living. Due to immobility and other clinical factors these patients are at high risk for developing pressure ulcers. As it is infeasible to gain written consent from this patient population and, due to the minimal risk of the study procedures, a waiver of individual authorization has been granted by Stanford University’s IRB (see Ethics approval section). Therefore, all patients over the age of 18 years admitted to one of the two ICUs will be enrolled in the study. Patients under 18 years of age, those with a known allergy to skin adhesive, or who possess a physical barrier preventing the application of the monitoring sensor, are not eligible for inclusion.

### Recruitment/Intervention

Upon admission to a study unit and as part of standard care, the patient receives a complete “head-to-toe” assessment of their skin. This is performed by two registered nurses (RNs). Any pre-existing pressure ulcer that is detected during this assessment is documented in the electronic medical record (EMR). After initial standard admission procedures are performed, and within the first hour of arrival, nursing staff will place a patient sensor (Leaf Healthcare, Pleasanton, CA, USA) in a predefined location on the patient’s chest (Fig. 2). If an exclusion condition is present, this will be documented and the patient will not be enrolled in the study and will not receive a patient sensor.

**Fig. 2 Fig2:**
[figure not shown]
Location of patient-monitoring sensor. *Used with permission from Leaf Healthcare, Inc.

For patients included in the study, the unit secretary will provide nursing staff with a patient sensor after associating the sensor’s serial number with the patient’s specific information. This is automatically derived from an Admission-Discharge-Transfer (ADT) data stream communicating directly with the Leaf Patient Monitoring System. At this time the unit secretary will open an envelope, pre-filled with the computer-generated randomized group allocation. A patient sticker will be affixed to the back of the randomization card and stored in a secure location for later retrieval and verification of correct randomization and enrollment. The patient will then be enrolled in either a treatment or control group.

When a subject is enrolled in the treatment group, the User-Dashboard will be turned “on,” allowing the sensor to communicate the patient’s position and movements (Fig. 3). The clinical team will review this information and be guided by visual displays to provide pressure ulcer-prevention turning practices. With the use of the User-Dashboard, nurses will be prompted to perform pressure ulcer preventative care, namely patient turning with satisfactory tissue decompression for 15 min, at least every 2 h (optimal). If a patient does not receive the full time of tissue decompression, the Leaf Patient Monitoring System automatically adjusts, proportionally reducing the time-to-next-turn. For example, if the patient was on their back and moved to their right side, but returned to their back within 7–8 min, the time-to-next-turn will be adjusted reciprocally from 2 h to 1 h. This ensures that patients receive at least 15 min of tissue decompression every 2 h.

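### The allocation envelope is opened when the sensor is handed over, before it is on the patient, so a late barrier or a failed placement can arise after the arm has been revealed

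*Protocol article*

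**What the plan says.** All references are to the Protocol article.

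- **Who may enter (Study population).** Entry is meant to be near-universal: "all patients over the age of 18 years admitted to one of the two ICUs will be enrolled in the study", under a waiver. Besides age and known adhesive allergy, the exclusions cover those "who possess a physical barrier preventing the application of the monitoring sensor, are not eligible for inclusion".
- **Exclusions and placement (Recruitment/Intervention, opening paragraph).** Two nurses examine the skin on admission. After the initial admission procedures and "within the first hour of arrival, nursing staff will place a patient sensor" at a predefined site on the chest. "If an exclusion condition is present, this will be documented and the patient will not be enrolled in the study"; the same sentence adds that such a patient gets no sensor.
- **Hand-over and envelope (Recruitment/Intervention, text after Fig. 2).** "For patients included in the study, the unit secretary will provide nursing staff with a patient sensor after associating the sensor’s serial number", which links it to that person's record. Then: "At this time the unit secretary will open an envelope, pre-filled with the computer-generated randomized group allocation". A patient sticker goes on the card, the card is stored, and "The patient will then be enrolled in either a treatment or control group".
- **What the allocation changes (same section).** Both arms wear the same sensor. The allocation decides only whether its data appear on the dashboard.
- **What depends on the sensor (Data management; Study endpoints, Primary).** Turning compliance, one of the two primary endpoints, is computed from the monitoring system's data.

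**The concern.** A nurse cannot apply a sensor that has not yet been handed over, and the envelope is opened at hand-over. On the written order, disclosure of the arm therefore comes before application. The physical-barrier exclusion is defined by whether the sensor can be applied, so in some patients it may be met only at the bedside. A sensor may also not get placed for other reasons.

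The trial is open label, and the unit's nursing staff both place the sensor and deliver the turning care being compared. A control patient's sensor shows them nothing they can use, so the incentive to persist with a difficult placement is not obviously equal between arms.

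Two things are at stake. Compliance is measured only in patients who wear a sensor, so unequal placement would make the two measured groups no longer comparable as randomized. The hospital-acquired pressure ulcer (HAPU) comparison would be affected as well if a patient found to have a barrier after the envelope was opened were handled as not enrolled.

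**Working it through.** **1. The order of events**

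| Step | Section | Arm revealed? |
|---|---|---|
| Admission skin check by two nurses | Recruitment/Intervention, opening paragraph | No |
| Exclusions already apparent: documented, no sensor given | same | No |
| Secretary registers the sensor and hands it over | Recruitment/Intervention, after Fig. 2 | No |
| Envelope opened at that time, card stickered and stored | same | Yes, to the secretary at least |
| Patient enrolled in an arm | same | Yes |
| Sensor placed on the chest, within the first hour | Recruitment/Intervention, opening paragraph | Can follow disclosure |

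Age, known allergy and a visible barrier can be settled in the first two rows. A barrier first met on application, or a sensor that is not placed, belongs to the last row. The text makes a patient included before the envelope and enrolled after it. It does not state that the exclusion check must be complete and recorded before opening.

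**2. The plan's own figure**

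Inputs from Sample size calculation: 5% versus 2.5%, two-sided 5% level, 80% power, equal groups. With a pooled variance under the null and mean rate 0.0375:

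n = [1.960·√(2·0.0375·0.9625) + 0.842·√(0.05·0.95 + 0.025·0.975)]² / 0.025² = (0.5266 + 0.2256)² / 0.000625 = 905.4, so 906 per group and 1812 in all.

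The stated size is reproduced, with power 80.0%. No allowance for loss is stated.

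**3. Illustration only: HAPU endpoint**

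The documents give no non-placement rate, so the fraction lost *d* and the HAPU risk *r* of those lost are assumed.

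*Equal loss in both arms.* Power at 906·(1 − d) per arm, for 5% versus 2.5%:
- d = 2%: 888 per arm, power 79%
- d = 5%: 861 per arm, power 78%
- d = 10%: 815 per arm, power 76%

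*Loss from one arm only, no true effect.* The remaining rate in that arm is (0.05 − d·r)/(1 − d):

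| d | r = 0% | r = 10% | r = 20% |
|---|---|---|---|
| 2% | 5.10% | 4.90% | 4.69% |
| 5% | 5.26% | 4.74% | 4.21% |

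For example, (0.05 − 0.05·0.20)/0.95 = 0.0421. The shift runs from +0.26 to −0.79 percentage points, against a planned difference of 2.5 points. Its sign depends on who is lost and from which arm.

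**4. Compliance endpoint**

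If a fraction *d* of one arm has no sensor, that arm's measured mean differs from its true mean by d times the gap in compliance between patients with and without a sensor. The documents give neither quantity, so no number is offered.

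**The case against.** **Eligibility comes first.** The sensor and envelope step is limited to patients already included, and excluded patients get no sensor. Being enrolled in an arm after the envelope reads naturally as assignment to a group, not as a second eligibility decision. This stands. A reader might infer that entry to the trial as a whole is decided with the arm known; the text does not support that. Enrolling every eligible adult under a waiver leaves little discretion.

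**A chest barrier would usually be seen at the admission skin check.** Probably so, which makes the residual group small. The check does not cover a sensor that cannot be fixed on the day or is not placed.

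**Nothing says the nurse sees the card before placement.** Correct: the secretary opens and stores it. A reader might infer that the nurse always knows the arm when applying the sensor. The text shows only that the arm has by then been revealed on the unit, with nothing described to keep it from the nurse.

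**There is an audit trail.** The Discussion describes daily monitoring and cross-checking of stickered cards against the allocation entered in the system. That can detect a wrong assignment and would help trace randomized patients. It is not described as checking whether a sensor was applied.

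**Larger error-rate figures can be produced.** If 2% to 3% of the treatment arm alone were dropped, all at 15% to 20% risk, the chance of a false result favouring treatment would rise from 2.5% to between 3.9% and 6.7%. The arithmetic is right. But it needs one-arm loss of patients at three to four times the average risk (15/5 to 20/5), and the incentive described under the concern points to the control arm instead. The opposite tail falls to between 1.5% and 0.8%, so total error is about 5.5% to 7.4%. The documents support none of these inputs.

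**Analysing everyone as randomized may be specified elsewhere.** It may be in a full protocol or analysis plan that is not shown, so its absence is not counted here. No section says that patients without a sensor leave the HAPU comparison.

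**Conclusion.** The point holds in a limited form. As written, the arm is revealed at sensor hand-over, before placement, so a barrier met on application or a failed placement can arise after disclosure in an open-label trial. The compliance primary endpoint is directly exposed, because it exists only where a sensor is worn. The HAPU comparison is exposed only if such patients are treated as not enrolled, which the article neither states nor rules out.

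The size cannot be established: no non-placement rate is given and the direction is unknown. The illustrated HAPU shifts are under one percentage point and rest wholly on assumed losses. This is a gap that costs little to close, not evidence that the trial's result would be wrong.

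**What to change.** Reorder the enrollment step in Recruitment/Intervention, in the text after Fig. 2:

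1. The secretary registers the sensor and hands it over with the display off for every patient.
2. Nursing staff confirm and document that no exclusion is present, including any physical barrier, and apply the sensor.
3. Only then does the secretary open the envelope, sticker the card and set the dashboard to the assigned arm.

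This works because both arms wear the same sensor and the allocation only sets the display. A patient in whom application fails is then excluded before randomization, with the arm unknown.

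The cost is a delay of minutes, within the first hour, before a treated patient's dashboard is switched on. No extra staff, procedures or patients are needed.

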**Fig. 3 Fig3:**
[figure not shown]
User-Dashboard – Leaf Patient Monitoring Interface. *Used with permission from Leaf Healthcare, Inc.

If the subject is enrolled in the control group, the unit secretary will turn the User-Dashboard “off” by selecting the “control patient” check-box in the Leaf Patient Monitoring System. This will turn the sensor information off and therefore not display any information to the User-Dashboard. Patients in the control group will continue to receive standard care practices, that is, pressure ulcer-prevention activities initiated by nurses using their usual care routines. Nursing care will not be “optimized” by the Leaf Patient Monitoring System, with the system withholding any data related to turning frequency, position schedule, and decompression time. The patient sensor will continue to collect these data for the purposes of research analysis only.

Each patient’s participation within the study begins within the first hour of arrival to a study unit and ends upon discharge or transfer from the study unit. Upon leaving the unit, the patient sensor will be removed and the patient will be discharged automatically from the Leaf Patient Monitoring System.

### Technology

The Leaf Patient Monitoring System is a proprietary system developed by Leaf Healthcare Inc. (Pleasanton, CA, USA) [10]. The Leaf Patient Monitoring System is a wireless monitoring system that enables personalized turning protocols. A wireless, wearable, single-patient sensor communicates a patient’s body position and movement, through a proprietary mesh network of relay antennas placed throughout the study units to a central monitoring system (Fig. 4). The Leaf Turn Management System accesses an industry standard Health Level Seven International (HL7)-ADT data stream. This allows for simplified and accurate patient enrollment and seamless tracking of patient movement throughout the study units. For data security, all data generated from the Leaf Patient Monitoring System are transferred and stored within the institution’s firewall to secure servers. The Leaf Turn Management System is the User-Dashboard that displays an individual patient’s positioning and movement data to the clinical team.

**Fig. 4 Fig4:**
[figure not shown]
Wearable patient sensor communication network. *Used with permission from Leaf Healthcare, Inc.

### Data management

Proprietary turning data will be acquired from the Leaf Patient Monitoring System. Compliance to preventative turning care will be defined by two measures. The first will sum the overall time the patient is overdue for turning care, divided by the total monitoring time, and will be reported as a percentile of time. For example, if a patient was on the unit for 4 h and did not receive preventative turning care at the second hour, but instead at the third hour (1 h overdue), then the patient’s care was in compliance for 3 of the 4 h of their length of stay. This would, therefore, represent a time in compliance of 75 %. If they received the turn on schedule, the compliance would be at 100 %. The second measure will divide a patient’s length of stay into 2 h turning blocks. In the above example, if the patient was turned once in their 4 h stay, compliance to turning would equal 50 %. Although we believe that the time in compliance is more appropriate than the proportion of turns within 2 h blocks, we will test and report on both measures as the latter reflects current clinical care practices.

### Pressure ulcer staging

The National Pressure Ulcer Advisory Panel (NPUAP) staging criteria will be used to stage all HAPUs [11]. Staging will be completed by an expert RN blinded to the patients’ study allocation. Adjudication will occur with the study team for any wounds that are difficult to stage.*Stage I, non-blanchable erythema*: intact skin with non-blanchable redness of a localized area usually over a bony prominence. Darkly pigmented skin may not have visible blanching; its color may differ from the surrounding area. The area may be painful, firm, soft, warmer or cooler as compared to adjacent tissue. Category I may be difficult to detect in individuals with dark skin tones. This stage may indicate “at risk” persons*Stage II, partial thickness skin loss*: partial-thickness loss of dermis presenting as a shallow, open ulcer with a red-pink wound bed, without slough. This may also present as an intact or open/ruptured serum-filled or sero-sanginous-filled blister. It presents as a shiny or dry, shallow ulcer without slough or bruising*. This category should not be used to describe skin tears, tape burns, incontinence-associated dermatitis, maceration or excoriation. *Bruising indicates deep tissue injury*Stage III, full-thickness skin loss*: full-thickness tissue loss. Subcutaneous fat may be visible but bone, tendon or muscle are *not* exposed. Slough may be present but does not obscure the depth of tissue loss. This *may* include undermining and tunneling. The depth of a category/stage III pressure ulcer varies by anatomical location. The bridge of the nose, ear, occiput and malleoli have no (adipose) subcutaneous tissue and category/stage III ulcers can be shallow. In contrast, areas of significant adiposity can develop extremely deep category/stage III pressure ulcers. Bone/tendon is not visible or directly palpable*Stage IV, full-thickness tissue loss*: full-thickness tissue loss with exposed bone, tendon or muscle. Slough or eschar may be present. This stage often includes undermining and tunneling. The depth of a category/stage IV pressure ulcer varies by anatomical location. The bridge of the nose, ear, occiput and malleoli have no (adipose) subcutaneous tissue and these ulcers can be shallow. Category/stage IV ulcers can extend into muscle and/or supporting structures (e.g., fascia, tendon or joint capsule) making osteomyelitis or osteitis likely to occur. Exposed bone/muscle is visible or directly palpable

